## Abstract

**Background:**

Hand fractures are common and sometimes require surgery to restore function. Placement of Kirschner wires (K-wires) is the most common form of surgical fixation. After placement, a key decision is whether to bury the end of a K-wire or leave it protruding from the skin (exposed). A recent systematic review found no evidence to support either approach and a national clinician and surgeon survey demonstrated further uncertainty. We aim to determine the design of a definitive randomised controlled trial assessing the cost and clinical effectiveness of buried versus exposed Kirschner wires for adults with metacarpal or phalangeal fractures.

**Methods:**

We will employ three methodologies: a national service evaluation of current clinical practice, patient and surgeon focus groups and a consensus meeting to finalise the protocol for a randomised controlled trial. For the service evaluation, all outcomes will be summarised using descriptive statistics overall and split by group (buried versus exposed K-wires). Information collected in the patient focus groups will be analysed thematically. The surgeon consensus meeting will address each part of the design in turn and through discussion agree a final protocol.

**Discussion:**

The study may be monitored, or audited in accordance with the current approved protocol, Good Clinical Practice (GCP), relevant regulations and standard operating procedures. The Chief Investigator will submit and, where necessary, obtain approval from the above parties for all substantial amendments to the original approved documents. A feasibility study report will be published by the Wire Study Steering committee. Additional members of the steering group and citable collaborators will be listed within the manuscript and their roles identified.

## Background

Hand injuries are common, with an estimated annual incidence of over 5 million injuries per year in the UK resulting in 250,000 operations, figures which continue to increase each year [1–5]. This is corroborated by Emergency Department statistics, which suggest that hand injuries account for over 20% of attendances [1, 2]. Furthermore, hand injuries are known to affect the younger, working population causing significant socioeconomic impact, as well as older patients where they disrupt daily activities of living and affect independence [6–8]. The optimal treatment of hand and wrist trauma was identified as one of the top ten priorities in the James Lind Alliance Priority Setting Partnership in September 2017 [9].

Fractures are one of the most common hand injures, accounting for approximately 19% of all fractures [2]. Most can be managed non-surgically, but a sizeable proportion undergo surgery. Closed reduction and percutaneous Kirschner wire (K-wire) fixation is the most common approach and is usually attempted within 2 weeks of injury under local, regional or general anaesthesia. Data from the British Society for Surgery of the Hand Open Fracture Audit indicates that around 70% of open hand fractures require K-wire fixation [10]. Following reduction of the fracture into an anatomical position, K-wires are passed across the fracture using a drill to hold the fragments in position. The surgeon then either shortens and bends the wire tip to leave it proud from the skin (exposed) or cuts them short and closes the skin over the wire (buried).

Whether K-wire ends should be buried or left exposed is an area of clinical uncertainty with substantial potential implications for the patient. A systematic review suggests a potentially higher rate of infection in exposed wires, but there is limited evidence to inform surgeon decision making [3]. We performed a national survey of clinicians and patients to further investigate this uncertainty. We found that those preferring to bury wires were motivated by reducing infection rates, whilst those preferring to leave them exposed cited ease of removal [4]. Surgeons also tailor their decision depending on patient characteristics. The clinical uncertainty is likely to have an impact on both patient and health economic outcomes, where the cost of removing a wire and the cost of infection must be weighed [5].

Before a randomised clinical trial can be conducted to answer this question, feasibility work is required. In particular, we need to know more about the variation in practice across the UK, so that we can ensure an RCT is feasible within the NHS. We also need to gather information about specific aspects of routine care, such as how and when patients are commonly followed-up, enabling us to minimise excess costs of a trial. Furthermore, information on the occurrence of infection will be useful in terms of sample size calculations for a future study. Once this information has been gathered, it can be used as a backdrop for feasibility discussions with both surgeons and patients to help refine the practical elements of a definitive RCT.

## Aims and objectives

### Aim

To determine the design of a definitive randomised controlled trial assessing the cost and clinical effectiveness of buried versus exposed K-wires for adults with metacarpal or phalangeal fractures in the hand.

### Objectives

To conduct a prospective service evaluation to determine:
○ The current clinical pathway of hand fracture patients undergoing K-wire fixation in the NHS○ The number of potentially eligible participants for a future RCT in K-wire fixation of hand fractures○ The number of K-wire fixation patients that attend routine follow-up○ The number of K-wire fixation patients that develop an infection to inform a sample size calculation for a definitive RCT○ The scope of the health economic evaluation needed in the trial to assess cost effectivenessTo explore acceptability and feasibility of a future RCT in K-wire fixation of hand fractures by conducting patient and surgeon focus groupsTo develop the outline of a definitive RCT through a consensus workshop process with surgeons

## Methods

This is a mixed-methods feasibility study consisting of three stages: firstly, a national service evaluation of current clinical practice; secondly, patient and surgeon focus groups; and thirdly, we will bring these strands together in a consensus meeting to finalise the protocol for an RCT.

### Stage 1: National service evaluation

This will be a trainee-led prospective national multi-centre service evaluation coordinated by members of the WIRE ‘Steering Committee’. Trainees from across the UK and abroad will be invited to participate in the study through the Reconstructive Surgery Trials Network (RSTN). All centres that treat patients with hand trauma will be invited to participate, with the aim of maximising the scope of feasibility information and engaging with units for future participation in the definitive trial.

A local collaborator(s) will be identified at each institution (Trainee Lead). Collaborators will be responsible for identifying a supervising consultant surgeon (or equivalent) and obtaining local approvals at their unit. If no trainees are available within a unit, consultants, associate specialists, specialty doctors, hand therapists or research nurses will be encouraged to participate and enter data and will be eligible for the same acknowledgement. Support will also be sought from other professional associations, including the British Society for Surgery of the Hand (BSSH) and the British Association of Plastic, Reconstructive and Aesthetic Surgery (BAPRAS).

Instructions for local registration and data collection will be provided for collaborators. This will include a PowerPoint presentation and accompanying video which can be presented to the staff body in order to explain the study being carried out. Each team will enlist an appropriate number of collaborators given the number of expected patients to be identified during the study period. The name and contact details of the supervising consultant and trauma coordinator (if available) will also, with their permission, be documented to allow for continuity should contact be lost with the local Trainee Lead. The study will be piloted at the Oxford University Hospitals NHS Trust and Buckinghamshire Healthcare NHS Trust prior to roll-out to ensure ease, accuracy and confidentiality of data capture and inform recruitment of collaborators.

#### Study participants

Study participants for the service evaluation will be all patients deemed to require surgery, undergoing K-wire fixation of an acute fracture(s) of the hand; involving the metacarpals and/or phalanges who present to the participating unit. In patients with bilateral hand fractures or multiple fractures on one hand requiring K-Wire fixation; data will be entered for all fractures as per one case maintaining each patient as the unit of analysis.

##### Inclusion criteria

Patients with primary K-wire fixation of open or closed fracture(s) of the metacarpals and/or phalangesAdults over 18 years oldMale or female patientsPrimary surgery within or at 2 weeks post injury

##### Exclusion criteria

Fixation strategies involving K-wires as part of an external fixatorNursing home residents, residential care residents or those serving custodial servicesPrimary surgery more than 2 weeks post injuryConcomitant wrist fracture or significant soft tissue injury

##### Data collection and entry

Data will be prospectively gathered and entered into the REDCap system. Login details will be supplied to collaborators once local permissions are confirmed in writing. Each patient will have a REDCap generated ID number assigned to them. This will be held locally alongside the patient hospital number. Only REDCap IDs will be held centrally. The full data dictionary is supplied in Appendix 1.

#### Clinical feasibility data

Patient demographicsDetails of surgical proceduresDetails of antibiotic treatmentsDetails of post-operative management and follow-upDetails of K-wire removal timing and location of wire removalUse of patient reported outcome measures (PROMs)Details of discharge from hand surgery serviceDetails of occurrence of post-operative infectionDetails of complications related to K-wire fixationDetails of further surgery required

These data will be collected for when the K-wire is in situ, at the time of removal and up to 30 days.

##### Data validation and quality assurance

It is expected that participating hospitals will enter a complete data set for all patients identified as having metacarpal or phalangeal fractures managed with buried or exposed K-wires within the service evaluation period. Following data collection, approximately 5% of the centre’s data sets will be randomly selected. The consultant supervisor at each centre will be contacted and asked to independently validate a proportion of the data. If concordance is <80%, a further data sample will be randomly selected. If concordance remains <80%, the centre will be excluded from the analysis. If concordance is >95%, the consultant supervisor will be contacted to ensure the independence of the validation process and a further data sample will be randomly selected.

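### The validation step checks the accuracy of records already entered and cannot show whether eligible patients were missed

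*Protocol article*

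**What the plan says.** The target population is complete by definition. Under Study participants, the service evaluation is meant to cover every patient who has an acute metacarpal or phalangeal fracture fixed with K-wires at a participating unit. The Data validation and quality assurance section states the same as an expectation of centres: "It is expected that participating hospitals will enter a complete data set for all patients identified as having metacarpal or phalangeal fractures".

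The check that follows works on a sample of records: "Following data collection, approximately 5% of the centre’s data sets will be randomly selected". The section next names who does the checking and on what: "The consultant supervisor at each centre will be contacted and asked to independently validate a proportion of the data". Two rules act on the result. At the low end, after a second sample has been tried: "If concordance remains <80%, the centre will be excluded from the analysis". The high end also leads to more sampling: "If concordance is >95%, the consultant supervisor will be contacted to ensure the independence of the validation process and a further data sample". The criteria for citable collaborators confirm the sampling frame, since they describe the supervisor's duty as validating 5% of entries.

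The Objectives ask Stage 1 for "The number of potentially eligible participants for a future RCT in K-wire fixation of hand fractures". A further objective concerns attendance: "The number of K-wire fixation patients that attend routine follow-up". Another is the count of infections, which is to feed the sample size of the definitive trial. Under Outcomes (Table 1 text), the eligible number is taken from observed patient throughput. At least 400 complete data sets is green, 200 to 400 amber, and fewer than 200 red.

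**The concern.** Concordance is defined only on records that exist. A patient who was never entered cannot be sampled, so omission leaves no trace in the result. A centre that enters every eligible patient but scores 79% on both samples is excluded. A centre that omits many patients and records the rest accurately is not picked up for the omission.

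This matters because Stage 1 is largely a counting exercise. Without an ascertainment figure, a reader of the results cannot tell low throughput from poor capture. Nor can the reader judge whether the infection and attendance percentages describe all K-wire patients or only those who were entered.

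**Working it through.** **The plan's own figure.** The article gives about 400 as the size of the definitive trial, without event rates, effect size, alpha or power. It cannot be reproduced, and this point does not depend on it. It is used below only as the stated green threshold.

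**What each safeguard can detect.**
- 5% sample and concordance rules: errors within entered records. Every consequence (resampling, exclusion, a query about independence) depends on concordance.
- Ten data sets of consecutive patients (criteria for citable collaborators): discourages selective entry, but covers ten data sets, is a condition for citation only, and has no stated check.
- Local spreadsheet linking hospital number to study number (Data recording and record keeping): its stated purposes are avoiding duplicates and supporting later follow-up entry. It lists patients already in the study.
- Prospective entry into REDCap (Data collection and entry): makes omission less likely but does not reveal it.

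None compares entries with a theatre log, trauma list or similar source.

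**Size, on assumed values.** The documents give no missed share and no rates. Let m be the share of eligible patients missed, taken as 10%, 20% and 30%.

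*Eligible number.* Entered = true × (1 − m). Assume 450 truly eligible and every entered record complete:
- m = 10%: 450 × 0.90 = 405 (green)
- m = 20%: 450 × 0.80 = 360 (amber)
- m = 30%: 450 × 0.70 = 315 (amber)

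To reach 400 records, the true number must be at least 400/0.90 = 445, 400/0.80 = 500 and 400/0.70 = 572 (rounded up).

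*Proportions.* True rate = p_entered × (1 − m) + p_missed × m. Hence observed minus true = m × (p_entered − p_missed): zero if the groups are alike, and of either sign if not.

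*Infection*, 5% assumed among entered patients:

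| m | Missed at 10% (twice the risk): true rate | Relative bias of the observed 5% | Missed at 2.5% (half the risk): true rate | Relative bias of the observed 5% |
|---|---|---|---|---|
| 10% | 0.045 + 0.010 = 5.5% | −9% | 0.045 + 0.0025 = 4.75% | +5% |
| 20% | 0.040 + 0.020 = 6.0% | −17% | 0.040 + 0.005 = 4.5% | +11% |
| 30% | 0.035 + 0.030 = 6.5% | −23% | 0.035 + 0.0075 = 4.25% | +18% |

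*Follow-up*, 90% assumed among entered and 70% among missed patients: the true rate is 0.81 + 0.07 = 88%, 0.72 + 0.14 = 86% and 0.63 + 0.21 = 84%. If missed patients attended more often, the sign would reverse.

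Concordance could be the same in every one of these scenarios, because m does not enter its calculation.

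**The case against.** The strongest reply is that a journal article condenses a fuller protocol, and that case finding may be covered in the collaborator instructions it mentions. That has some weight. But the article sets out the validation step in detail (sample, validator, thresholds, consequences), and the point concerns what that stated step can detect.

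A second reply is that the design already works against selective omission. Records are meant to be opened prospectively, before attendance or infection is known, and citation requires consecutive patients. This stands as a reason to expect less bias, though it gives no measure of capture.

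A third is that undercounting errs on the safe side: missed patients cannot produce a false green at 400. That is correct for the progression criterion. It does not help the proportions, which can err either way.

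Three stronger readings are tempting but not supported:
- A reader might infer that the citation rule of at least 95% complete data sets encourages leaving out non-attenders, so that attendance and infection are biased upward. The article does not define how completeness is counted, the data dictionary is not shown, and non-attendance may itself be a recorded value. The direction of bias is unknown.
- A reader might infer that a centre simply passes at 100% concordance. In fact anything above 95% prompts contact with the supervisor and a further sample. That sample is again one of data, so it does not address capture.
- A reader might infer that this is the only quality control. There is also a two-trust pilot, validated data entry with audit trails, and data queries. None is described as testing ascertainment.

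**Conclusion.** The point holds as a limited design weakness. The validation step measures accuracy and is blind to capture, while Stage 1 objectives and one progression criterion depend on capture. The effect on the eligible number and the data-set count is certain in direction (downward) whenever anyone is missed. The effect on infection and follow-up proportions is conditional on missed patients differing from entered ones, and can go either way.

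For missed shares of 10% to 30%, the illustration gives relative bias in the infection rate from −23% to +18%, and zero if the groups are alike. These figures rest entirely on assumed missed shares, rates and risk ratios. They show what concordance cannot exclude, and do not estimate what will happen. This is a worthwhile, inexpensive improvement to a feasibility study and does not invalidate it.

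**What to change.** Add a case-ascertainment count to the existing validation step:

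1. For a randomly chosen part of each centre's data collection window, the supervising consultant, or the trauma coordinator where there is one, lists metacarpal and phalangeal K-wire cases from the theatre or trauma log.
2. Screen these cases against the article's inclusion and exclusion criteria. A raw log count would overstate eligibility, because time since injury, residential or custodial status and associated injuries may need a look at the notes.
3. Compare the screened list with the REDCap entries, using the local linkage spreadsheet, and report entered over eligible for each centre beside concordance.
4. Give the eligible number both as entered and corrected for ascertainment. For example, 360 entered at 80% ascertainment gives 360/0.80 = 450. This assumes the log is itself complete and the sampled period is typical.
5. Repeat the infection and follow-up summaries in centres above an ascertainment level fixed before the data are seen. The documents offer no basis for a particular cut-off, so the steering committee should choose and state one.

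The cost is some collaborator time for the log count and brief note review, plus one sensitivity table. No patient procedure or central transfer of identifiable data is needed, since the matching is done locally and only counts are reported.

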##### Data analysis plan

All data will be collated and managed centrally on a REDCap database. Data reports will be exported to an appropriate statistical software platform for analysis. We will perform descriptive analyses for all

### Stage 2: Patient and public involvement—focus groups

The patient focus groups aim to explore patient perspectives on the study in more detail. These will be semi-structured in nature. Likely topics to be discussed will include:
Experience of K-wire fixation and postoperative rehabilitationTreatment expectationsConsent process and recruitment to a trialPrioritising outcome measuresDiscussion of proposed trial design

The focus group will be facilitated by members of the study team with experience of running patient focus groups. They will not be part of the surgical community. Patients with experience of either buried or exposed K-wires will be invited to the focus groups. They will be recruited from regional hand surgery units and through advertising via the NIHR INVOLVE network. We will adopt maximum diversity sampling in selecting participants for the focus groups. The focus groups will have no more than eight participants in each session, and we aim to run three groups to achieve a thematic data saturation within funding and time constraints. The focus groups will not be recorded, but minutes will be recorded by a facilitator. The minutes will be circulated to the participants for verification. Patients will be reimbursed expenses in line with NIHR INVOLVE costings.

### Stage 3: Consensus meeting

Engaging the surgical community in agreeing the final details of the study protocol will be essential for a successful study. Surgical trials can be difficult to undertake, especially if surgeons remain uncertain about the objectives of the trial and treatment arms involved. The aim of the meeting is to achieve consensus within the surgical community regarding vital aspects of the trial design. We will invite the following stakeholders:
Collaborators who have contributed to the service evaluation (stage 1)Patients and surgeons that take part in the focus groups (stage 2)Principal investigators of existing relevant research groupsMembers of key national societies:
○ The British Society for Surgery of the Hand○ The British Association of Plastic, Reconstructive and Aesthetic Surgeons○ The British Orthopaedic Association○ The Orthopaedic Trauma Society

We will present outputs from the first two stages of this study and will discuss the following points, with an anonymous voting process to reach consensus:
Types of injury to be included in the trial, e.g. open vs. closedTypes of treatments to be included, e.g. single K-wire vs. external fixation framesChoice of primary outcome: infection, e.g. how it should be measuredOther outcomes to be included, e.g. choice of PROM

The results of the consensus meeting will be collated and summarised by the steering group and published in an appropriate peer-reviewed journal.

### Study activities

#### Informed consent

No formal recording of consent is needed for this study. Stage 1 is a service evaluation collecting routine data and does not need patient consent. No changes in practice are occurring, no randomisation of treatment is occurring, and results will not be used to generalise to other patients. Patients and surgeons will imply consent by attending a focus group or consensus meeting.

#### Discontinuation or withdrawal from study

All participants have the right to withdraw from the study at any time. Those participants withdrawing will be offered two options: either to withdraw all of their data from the study (where it can be identified and removed) or to allow their data to be kept for inclusion in any analysis.

